### Cluster randomisation of clinics

Clusters of hospitals will be determined based on number of beds and number of medical oncologists to increase comparability of hospitals and to reduce contamination [64]. Of each pair, one hospital will be randomly allocated to the intervention condition and the other to the control condition. Randomisation took place after all hospital boards and medical oncologists had agreed to participate. Next, an independent statistician allocated to the intervention or control condition based on clusters by selecting three closed envelopes (Figure 1). Patients will be invited to take part by their medical oncologist or research nurse.

### Statistical analysis

To measure the effect of the implementation the PMI and NRS will be used and tested with general linear model analysis of variances (GLM ANOVA) repeated measures. Qualitative content analysis will be used to analyse the results of the focus group discussions and to analyse the interviews to evaluate the SMS alert intervention. Qualitative analysis will be supported by the use of the Atlas.ti software programme.

Data collected via SMS-IVR will be analysed for descriptive data: how did pain scores change and fluctuate in the whole period, what actions were taken by the research nurse, and did this intervention help the patients to manage pain? Subgroup analysis will be conducted. Differences in subgroups of the effectiveness of the intervention are expected. Subgroups will be classified by: age, gender, race, education, performance status, and classification of malignant tumors (TNM stage). The most recent version of SPSS will be used to perform the statistical analysis.

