**Figure 1 F1:**
[figure not shown]
**Flowchart cluster randomisation of clinics**. Figure 1 shows the cluster randomisation of clinics. A cluster RCT with two arms will be performed in six oncology outpatient clinics of hospitals, with three hospitals in the intervention and three in the control condition. Clusters of hospitals will be determined based on number of beds and number of medical oncologists. We require 35 patients per hospital, a total of 210 patients.

1. Training of oncologists and nurses involved in cancer care on the most important aspect of the CPG comprising of three one-hour sessions, one main session at baseline, session two at month six, and the final session at month twelve (intervention arm).

2. Patients will receive SMS-IVR and personal advice by phone on how to reduce their pain if their pain rating is 5 or higher on a numeric rating scale (NRS) of 0 (no pain at all) to 10 (worst pain you can imagine) (intervention arm).

3. Patients will receive a leaflet on cancer pain of the Dutch Cancer Society (in both arms).

4. Oncologists and nurses will receive a leaflet for professionals on pain treatment of the Comprehensive Cancer Centre organisation (VIKC) (both arms).

5. GPs in the Netherlands will be offered a web-based training on the most important aspects of the CPG (intervention arm).

Follow-up measurements in all hospitals will be conducted to study the long-term effect of the intervention. Regarding the patients recruited in this study, the intention to treat principle will be used (Figure 2).

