### Intervention

The intervention was based on a pilot study with 13 patients, performed from November 2009 to January 2010, to test feasibility of SMS-IVR. The mean response rate was 62%. A significant reduction of highest pain intensity was found between pre- and post-test (p = 0.018). Pain fluctuated more in patients included in this pilot study than would be expected in patients who will be included in the present study, because only patients in palliative care were included in the pilot study.

Next, we developed a multifaceted intervention with hospital as cluster. Multifaceted interventions are proven to be more effective than single interventions [66,67]. Oncologists and nurses in the hospitals allocated to the intervention condition will be trained in-person, and GPs of patients that take part in the study will be offered a web-based training on the most important aspects of the CPG. Patients in the intervention condition will get SMS-IVR and will receive a personal advice by phone how to reduce their pain if their pain rating is 5 or higher on a NRS of 0 (no pain at all) to 10 (worst pain you can imagine). The research nurse of the hospital, specialised in pain treatment and trained for this project, will provide the personal advice.

The training for oncologists and nurses consists of three one-hour sessions, all given in-person; one main session at baseline, session two at six months, and the final session at 12 months. The first session will include the aim of the study, the main aspects of pain treatment in patients with cancer, pain measurement, and an instruction of the SMS-IVR system in detail. The next two sessions aim to summarise the first session and discuss problems associated with the implementation of the guideline.

Figure 3 shows the workflow of the SMS-IVR intervention. Patients receive SMS-IVR minimal once a week (Tuesdays), twice a day, during 12 weeks (Figure 2). SMS alerts are used as a reminder that they will receive an automatic telephone call 15 minutes later with IVR. SMS alerts will be received at 09:45 a.m. and at 2:45 p.m. At 10 a.m. and at 3 p.m. the patients will be called and invited to rate their pain on a scale of 0 (no pain) to 10 (worst pain imaginable). Morning: Rate your pain by choosing a number that best describes your WORST pain in the last 24 hours. Afternoon: Rate your pain at this moment.

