### Primary and secondary outcome and measurement instruments

The primary outcomes of this implementation study include:

The first primary outcome is the percentage of all patients that visit the medical oncology outpatient clinic with adequate pain therapy/medication. Pain treatment adequacy will be calculated with both the Cleeland's Pain Management Index (PMI)[68] and Ward's variation of the PMI [33]. It is the most used measure for adequate pain treatment [33]. Cleeland's PMI compares the most potent analgesic prescribed, with patient's reported worst pain level on the Brief Pain Inventory (BPI). In addition, Ward's variation of the PMI compares the most potent analgesic used by a patient used with that patient's reported worst level of pain on the BPI. The worst score on the BPI will be determined (1 to 3, mild pain; 5 to 6, moderate pain; and 7 to 10, severe pain), where the absence of pain will be defined as 0, mild pain as 1, moderate pain as 2 and severe pain as 3. The worst score on the BPI is used because it is often used clinically as an indicator for treatment [69]. PMIs will be computed by subtracting the pain level from the analgesic level, ranging from -3 (a patient with severe pain receiving or using no analgesic drug) to +3 (a patient with no pain receiving or using a strong opioid or equivalent). PMI-scores of 0 or higher are considered to be a reflection of adequate pain treatment, whereas negative PMI-scores are considered to reflect inadequate pain treatment.

The second primary outcome is the mean pain intensity of cancer patients, measured with an NRS (SMS alerts and pain diary). The NRS is the most appropriate choice to use in practice for pain intensity [70,71] (see Table 1). The pain dairy is used to obtain additional information (medication use, side effects of medication) and to report pain intensity in the control group.

**Table 1 T1:** Validated patient questionnaires/scales used in this study

Measurement	Validated questionnaires	Time points (M = month)
**Pain intensity**	A. Numeric Rating Scale (NRS) B. Brief Pain Inventory Short form (BP-SF)	A. M0-M3/M9/M15 B. M0/M3/M9/M15

**Multidimensional aspects of pain**	McGill pain questionnaire (MPQ)	M0/M3/M9/M15

**Pain interference with function**	Brief Pain Inventory Short form (BP-SF)	M0/M3/M9/M15

**Adequate pain treatment**	Ward's Pain Management Index (PMI-revised)	M0/M3/M9/M15

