### Sample size

Sample size calculations of the present study with three clusters of two hospitals, are based on the expected effect of the intervention on the PMI. However, the present study is the first investigating the effects of using an SMS-IVR system in cancer pain management. Several studies show that adequate pain relief can be achieved in 70 to 90% of patients with cancer [44-47]. To achieve this, the present study aims to find out whether our implementation strategy reduces the negative PMI from 42% [6] to 20% [44-47] of all cancer patients visiting the outpatient clinic.

To detect a difference with 80% power (alpha = 0.015), we need 90 patients per condition. Accounting for clustering resulted in an intraclass correlation coefficient (ICC) of 0.015. Based on the ICC and three hospitals per condition, we need 30 patients per hospital. Taking into account a dropout rate of 15%, we need 35 patients per hospital, for a total of 210 patients.

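### Repeated-measures ANOVA does not match the percentage on which the trial is defined and sized, by default drops incomplete patients despite intention to treat, and names no term for hospital

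*Protocol article*

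**What the plan says.** The Statistical analysis section states that "the PMI and NRS will be used and tested with general linear model analysis of variances (GLM ANOVA) repeated measures". On software it adds: "The most recent version of SPSS will be used to perform the statistical analysis". It does not say which time points are levels of the model, whether the PMI enters as a score or as adequate/inadequate, which effect is tested, or how missing assessments are handled. It names no hospital term.

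Other sections of the same article fix what this analysis has to serve:

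- **Outcome.** "The first primary outcome is the percentage of all patients that visit the medical oncology outpatient clinic with adequate pain therapy/medication". The cut-off is on a score from -3 to +3: "PMI-scores of 0 or higher are considered to be a reflection of adequate pain treatment". The second primary outcome is mean pain intensity on the NRS.
- **Schedule.** Table 1 places the PMI at M0, M3, M9 and M15.
- **Sample size.** Negative PMI 42% versus 20%, 80% power, alpha 0.015, 90 patients per condition, ICC 0.015, 15% dropout, 35 per hospital, 210 in total.
- **Design.** Six hospitals in three pairs, one of each pair allocated to each condition.
- **Analysis principle.** "Regarding the patients recruited in this study, the intention to treat principle will be used".

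**The concern.** The article makes a positive choice of model, and an analysis plan that followed it would inherit three problems.

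1. The test compares means, while the outcome is defined and powered as a proportion. A trial could show a difference in mean PMI without a difference in adequacy, or the reverse.
2. SPSS GLM repeated measures deletes by default any patient with a gap at any within-patient level. In cancer patients followed for 15 months, the gaps will include deaths and deterioration. Deletion conflicts with analysing the patients as recruited, and it discards values that were observed.
3. Hospitals were randomised. A model that treats patients as independent understates the standard error of the group effect.

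**Working it through.** **Step 1. Reproduce the planned size.** Inputs from the Sample size section: p1 = 0.42, p2 = 0.20, power 0.80, alpha 0.015 (taken as two-sided; sidedness is not stated).

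n = (z(0.9925) + z(0.80))² × [p1(1 − p1) + p2(1 − p2)] / (p1 − p2)²

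= (2.432 + 0.842)² × (0.2436 + 0.1600) / 0.0484 = 89.4, so 90 per condition.

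The stated figure is reproduced exactly by an unpooled two-proportion formula with no design effect. The planning quantity is therefore a proportion.

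**Step 2. Score mean against percentage.** Two constructed arms show that the mean does not carry the percentage:

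- Arm A: 42% at -1, 58% at +1. Mean = -0.42 + 0.58 = 0.16.
- Arm B: 20% at -1, 44% at 0, 36% at +1. Mean = -0.20 + 0 + 0.36 = 0.16.

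The difference in negative PMI is the full planned 22 points, and the difference in means is zero. Conversely, moving patients from 0 to +2 raises the mean and leaves adequacy unchanged.

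**Step 3. Yes/no form under a normal model.** In 20,000 simulated trials (90 per arm, one time point, no clustering), a t-test on 0/1 data at nominal 0.05 rejected in 0.048 of trials when both arms were at 42%, and in 0.050 when both were at 20%. In this simple case, error control is not the problem.

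**Step 4. Complete cases.** Power is from the two-proportion test with pooled variance under the null hypothesis, before clustering. This is why it is 0.78 rather than 0.80 near n = 90.

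| Loss | Complete patients | Per arm | Power, alpha 0.015 | Power, alpha 0.05 |
|---|---|---|---|---|
| 15% overall (stated) | 210 × 0.85 = 178.5 | 89.25 | 0.78 | 0.90 |
| 15% at each of three follow-ups (assumption) | 210 × 0.85³ = 129.0 | 64.5 | 0.61 | 0.78 |

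In the second row, if patients who leave do not return, 178.5 have an M3 value. About 178.5 − 129.0 = 49.5 of them would be deleted although M3 was observed.

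**Step 5. Hospital.** With the stated ICC, the design effect is 1 + (30 − 1) × 0.015 = 1.435 at 30 patients per hospital, and 1 + 34 × 0.015 = 1.51 at 35. If hospital is ignored, the true error of a nominal two-sided test is about 2 × [1 − Φ(z/√DE)]:

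- nominal 0.05: 1.960/√1.435 = 1.636, giving 0.10 (0.11 at 35 per hospital);
- nominal 0.015: 2.432/√1.435 = 2.031, giving 0.042.

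This applies to a comparison of groups at one time point. For a group-by-time contrast the relevant ICC is that of change, which the article does not give.

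**Step 6. Which patients.** The first primary outcome is worded for all clinic visitors. The Figure 2 legend describes four one-week measurements of whoever attends. Those are different samples of people, so a within-patient model does not fit them. It can apply only to the recruited patients.

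**The case against.** The strongest reply is that an article condenses. Imputation before the ANOVA, a hospital factor and the coding of the PMI could all stand in a fuller protocol or analysis plan, and their absence here is not in itself a fault. That is fair, and it limits the second and third parts: imputation would soften the deletion problem, and a hospital term could be added. It does not remove the first part, because a named test of means still sits against an outcome defined and sized as a percentage. If the 0/1 form is used, the group means are the percentages and the simple simulation shows almost no error inflation, so the charge of a wrong distribution carries little weight on its own. It also does not touch the NRS.

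At the plan's own 15% loss, about 178 patients remain against a planned 180, so deletion then costs almost no power. What remains is a selection bias of unknown size.

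Two stronger readings are tempting:

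- **M0 counted as an outcome.** A reader might infer from Table 1 that M0 is a level of time and that the effect is diluted (for example, 22 points to 22 × 3/4 = 16.5 in a group main effect over four visits). Table 1 lists measurement times, not model terms. The analysis section announces no main-effect test, and a group-by-time test is not diluted in this way. M9 and M15 are there by design, to study the long-term effect.
- **Almost no complete diaries.** A reader might treat the 24 diary ratings as levels and apply the pilot's 62% response. The article does not make the ratings levels. The outcome is mean pain intensity, which can be an average over available entries. The 62% is an SMS-IVR response rate from 13 palliative patients, not a diary completion rate.

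**Conclusion.** The point stands in three parts. First, the named ANOVA does not clearly test the percentage that defines and sizes the trial. The fault is mainly this mismatch, not error inflation. Second, by default the procedure conflicts with the stated intention to treat. The cost in power runs from negligible at the stated 15% loss to a fall from about 0.78 to 0.61 if 15% were lost at each follow-up. Both figures are at alpha 0.015 as printed and before clustering, and the second rests on an assumed loss pattern. The accompanying bias cannot be sized, because the article gives no mortality or loss by arm. Third, no term for the randomised unit is named. With the stated ICC, ignoring hospital would roughly double a nominal 0.05 error for a single-time comparison.

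The documents do not support saying that M0 is analysed as an outcome, or that diary gaps would remove nearly all patients. The sentence should be changed before analysis.

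**What to change.** Replace the single ANOVA sentence with the following.

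- **PMI, recruited patients.** Analyse PMI of 0 or higher with a logistic mixed model (random effects for hospital and patient) or, as an alternative, GEE clustered on hospital, which has no random effects.
- **NRS, recruited patients.** Use a likelihood-based linear mixed model on all available values.
- **Both.** Account for hospital and its pairing, with a small-sample correction for six clusters. Take M0 as a covariate and name the primary time point in advance. If M0 is kept as a level of time, the effect must be the group-by-time contrast, not the group main effect.
- **Analysis set.** Include every recruited patient with available data in the assigned arm. Report deaths and missing data by arm, with a sensitivity analysis for missing values.
- **One-week samples of clinic visitors.** Analyse these separately as cross-sectional data with hospital as cluster.

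No new data or visits are needed. The cost is somewhat more modelling work, in the same software provided the chosen small-sample correction is available there.

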**Methods/design:**

A cluster randomised controlled trial with two arms will be performed in six oncology outpatient clinics of hospitals in the Southeastern region of the Netherlands, with three hospitals in the intervention and three in the control condition. Follow-up measurements will be conducted in all hospitals to study the long-term effect of the intervention. The intervention includes training of professionals (medical oncologists, nurses, and general practitioners) and SMS-IVR to report pain in patients with cancer to improve pain reporting by patients, pain management by medical oncologists, nurses, and general practitioners, and decrease pain intensity.

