### Study design

A non-blinded cluster RCT, will be performed in six oncology outpatient clinics of hospitals in the Southeastern region of the Netherlands, with hospital as cluster. Stratified randomisation will be performed based on pairs of two comparable hospitals regarding number of beds and number of medical oncologists. For each pair, one hospital will be randomly allocated to the intervention condition and the other to the control condition. Allocation to the intervention or control condition will be done before start of the intervention period by asking a statistician to select three closed envelopes (Figure 1). The allocation was generated by an independent statistician. Chosen implementation strategies are:

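### The named primary analysis, GLM repeated-measures ANOVA, makes no stated provision for hospital clustering or matched pairs, although six hospitals are randomised in three pairs

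*Protocol article*

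**What the plan says.** The Study design section describes the trial as follows: "A non-blinded cluster RCT, will be performed in six oncology outpatient clinics of hospitals", "with hospital as cluster". The abstract gives the split: "with three hospitals in the intervention and three in the control condition". Study design and Cluster randomisation of clinics both say that hospitals are first paired on number of beds and number of oncologists, and that one of each pair is then drawn for the intervention.

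The Sample size section acknowledges correlation within hospitals: "Accounting for clustering resulted in an intraclass correlation coefficient (ICC) of 0.015". It continues: "Based on the ICC and three hospitals per condition, we need 30 patients per hospital". After an allowance for dropout this becomes 35 per hospital and 210 in all.

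The Statistical analysis section gives one method for the two primary outcomes. The PMI and the NRS are to be "tested with general linear model analysis of variances (GLM ANOVA) repeated measures". It does not list the factors, the error term or the degrees of freedom. Neither this section nor any other mentions a hospital effect, a cluster-robust standard error, an analysis of hospital summaries or a pair term. The nearest hint is in Objectives/hypothesis, which speaks of reducing pain at individual and cluster level. That is an aim, not a method.

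**The concern.** When hospitals are randomised, the arm effect has to be judged against variation between hospitals. There are three per arm, which leaves 4 degrees of freedom, or 2 if the pairs are respected. Repeated-measures ANOVA with arm as the between-subjects factor judges it against variation between patients. With 180 patients analysed, that is 180 - 2 = 178 degrees of freedom. The repeated factor deals with several measurements on the same person. It does nothing for the likeness of patients treated in the same clinic.

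If the named method is applied in its ordinary form, standard errors are too small wherever hospital differences enter the comparison. A difference among a few hospitals could then be reported as an effect of the intervention on either primary outcome. A later analysis plan that follows the article would carry the problem forward.

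**Working it through.** **Inputs.** All are from the Sample size section: ICC 0.015; 30 analysed and 35 recruited per hospital; three hospitals per arm; negative PMI 42% versus 20%; alpha 0.015; power 80%. The article does not say whether alpha is one- or two-sided. Two-sided is assumed here, and nominal 5% is shown alongside.

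**1. The plan's own figure.** Two proportions, unpooled variance, two-sided 0.015, no design effect:

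n = (2.432 + 0.842)² × (0.42×0.58 + 0.20×0.80) / 0.22² = 10.72 × 0.4036 / 0.0484 = 89.4, so 90 per arm, or 3 × 30.

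At the stated alpha, 90 is thus reached without any allowance for clustering. This is not the only route. A one-sided 0.05 test with continuity correction needs 63, and 63 × 1.435 = 90.4, but that is not the alpha the article states. Either way, sample size alone does not protect the type I error. The analysis has to.

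**2. Between-arm comparison at one time point or averaged over time.**

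- Design effect: DE = 1 + (m - 1) × ICC = 1 + 29 × 0.015 = 1.435.
- True SE / patient-level SE = √1.435 = 1.198. Intervals are 1 - 1/1.198 = 17% too narrow, before the critical value changes from 1.96 to 2.78 (t on 4 df).
- Actual type I error = 2 × [1 - Φ(z / √DE)].
  - Nominal 5%: z = 1.960, 1.960/1.198 = 1.636, giving 10.2%.
  - Nominal 1.5%: z = 2.432, 2.432/1.198 = 2.030, giving 4.2%.

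With all 35 per hospital, DE = 1.51 and the rates are 11.1% and 4.8%.

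Simulation with three hospitals per arm, 30 patients each and no effect agrees. A normal outcome gives 10.1% and 4.2%. A binary outcome at 31% or 42% gives 10.1 to 10.3% and 4.1 to 4.2%. For the normal outcome, a t-test on the six hospital means holds 4.9% and 1.4%.

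Other ICC values (assumptions, except 0.015):

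| ICC | Nominal 5%, m = 30 to 35 | Nominal 1.5%, m = 30 to 35 |
|---|---|---|
| 0.005 | 6.7 to 7.0% | 2.3 to 2.5% |
| 0.015 | 10.2 to 11.1% | 4.2 to 4.8% |
| 0.03 | 15.2 to 16.8% | 7.5 to 8.7% |

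**3. Arm-by-time (change) comparison.** Stable hospital differences cancel in a change score. Let r_h be the correlation of hospital effects between time points and r_p the within-patient correlation. The article gives neither, so both are assumed. The ICC of the change is 0.015(1 - r_h) / [0.015(1 - r_h) + 0.985(1 - r_p)], and DE = 1 + 29 × that value. Type I error at nominal 5%:

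| r_h | r_p = 0.3 | r_p = 0.5 | r_p = 0.7 |
|---|---|---|---|
| 0 | 12.3% | 15.0% | 20.6% |
| 0.5 | 8.7% | 10.2% | 13.5% |
| 0.9 | 5.7% | 6.0% | 6.7% |
| 1 | 5.0% | 5.0% | 5.0% |

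**4. Power of a hospital-level analysis, 30 per hospital.** SE = √(0.4036 × 1.435 / 90) = 0.0802, so the non-centrality is 0.22 / 0.0802 = 2.74. From the non-central t distribution:

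| Analysis | Alpha 0.05 | Alpha 0.015 |
|---|---|---|
| Unpaired, 4 df | 55% | 27% |
| Paired, 2 df, no gain from matching (assumed) | 34% | 12% |

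**The case against.** The strongest reply is that one sentence naming a family of methods is not a model specification. It lists no factors and no error term, and it does not exclude a hospital or pair factor. The article plainly knows that its design is clustered. The Ethical considerations section refers to an approved research protocol, which is not shown, and a condensed article may leave model terms to such a document. This stands to the extent that the article cannot be said to declare patients independent, or to fix 178 degrees of freedom. It does not dispose of the point. The method that is named deals with within-patient correlation only. Adding hospital as a further factor would help only if hospitals within arm became the error term for the arm effect.

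A reader might also infer that the false-positive rate doubles at 5% and nearly triples at 1.5% whatever test is used. The documents do not support that. Those multiples belong to a between-arm comparison at one time point or averaged over time. Table 1 includes a baseline measurement, and the article does not say whether the arm effect or the arm-by-time effect decides. If it is the latter, the inflation may be nil or may exceed a doubling. Effective matching, or an ICC below 0.015, would also reduce it.

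**Conclusion.** The point holds as a mismatch between a named method and the design: hospitals are randomised in pairs, the plan itself expects correlation within hospitals, and the stated analysis of both primary outcomes provides for neither.

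Its size depends on the comparison. With patients as the error term, ICC 0.015, 30 per hospital and no gain from matching, a between-arm test at one time or averaged over time rejects a true null about 10% of the time at nominal 5%, and about 4% at nominal 1.5%. For an arm-by-time test the rate at nominal 5% lies between about 5% and about 21% under the assumed correlations. The article gives no basis for choosing within that range. It should be put right before the data are analysed.

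**What to change.** Replace the sentence on GLM ANOVA with an analysis that has hospital as the unit of inference.

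- **NRS:** a linear mixed model with random effects for hospital and for patient within hospital, using Kenward-Roger or Satterthwaite degrees of freedom.
- **PMI:** a test on the six hospital summaries, or a logistic mixed model or GEE with a small-sample correction.
- **Both:** say which contrast is decisive (arm at a time point, averaged, or arm by time), state in advance whether the matched pairs enter the model (2 df) or not (4 df), and report the estimated ICC.

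The wording change is cheap, and SPSS, the software named, has mixed models. The consequence is not small. Intervals on 4 df are about 1.198 × 2.78/1.96 = 1.70 times as wide as the patient-level ones at ICC 0.015. The stated 80% power has to be restated, to about 55% at alpha 0.05 or 27% at 0.015, and lower still if paired with no gain from matching. That loss comes from having six hospitals. A patient-level analysis would conceal it, not avoid it.
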